#### Entomological

Transmission parameters in the two study arms will be estimated from measurements made throughout the transmission season.

Primary endpoint: the EIR for *An. gambiae* s. l. and *An. funestus* s. l. estimated as the mean number of sporozoite infective bites/person/year.

Secondary endpoints: (i) the relative abundance of outdoor host-seeking *An. gambiae* s. l. and *An. funestus*; (ii) host feeding preferences of *An. gambiae* s. l.; (iii) changes in frequency (% mortality using diagnostic dose) and strength (LD_50_ and resistance ratio) of insecticide resistance to alphacypermethrin, permethrin, non-pyrethroid insecticides in each study arm; (iv) ITWL bioefficacy and durability over 12 months.

### Sample size rationale

#### Epidemiological

LLINs can reduce malaria morbidity by approximately 40–70 % [3]; the impact of ITWL alone or in combination with LLINs on malaria is unknown. The effects may be additive or synergistic (e.g. by having a mass killing effect and/or reducing mosquito longevity) or antagonistic (e.g. if the LLINs are repellent thereby reducing mosquito house entry and contact with ITWL). Due to the intensity and projected cost of the ITWL intervention, a minimum reduction in malaria of 30 % is considered of public health importance.

For the cohort study, sample size is based on annual cumulative incidence of malaria infection in each study arm as the primary outcome. From baseline surveys conducted in Muheza, it was assumed that cumulative incidence of malaria would be 2.5–3.0 detected episodes/year, with a coefficient of variation (CV) between clusters of 0.302 and an intra-cluster correlation (ICC) of 0.047. Therefore with 22 clusters per arm, sampling an average of 110 children (assuming 18 % loss to follow-up) per cluster, the study will have >85 % power to detect a 30 % reduction in malaria incidence at the 5 % significance level [59].

To measure time to first malaria episode during the evaluation year, assuming an ICC of 0.047, for a cumulative incidence of 2.0 episodes/year, the monthly risk would be 0.167. Using a binomial distribution calculation, the probability of having zero positive determinations (i.e. of ‘surviving’ malaria-free) over 1 year is (1–0.167)^12^ = 0.112; with a monthly 30 % reduction in risk, the cumulative probability of having no monthly positive RDTs in 12 months in the intervention arm would be (1–0.117)^12^ = 0.226. Sampling from 44 clusters with 90 children per cluster, the study will have 99 % power to reject the null hypothesis of no difference in ‘survival’.

To assess the effectiveness of the interventions on anaemia in children aged 6 to 59 months, assuming mean haemoglobin of 10.75 g/dl, 22 clusters in each study arm and a CV of 0.048, the study will be able to detect a difference of 0.5 g/dl in mean haemoglobin with 5 % significance and 85 % power between the study arms, sampling an average of 45 children per cluster.

#### Entomological

Monitoring of indoor mosquito density will be conducted bi-monthly in eight different randomly selected households from six clusters per study arms (total of 576 households). All anopheline mosquitoes from each household will be randomly chosen for analysis (speciation, sporozoite ELISA, *kdr* resistance status and blood meal source).

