### Design

A parallel cluster randomized controlled study design will be used as ITWL is a community-level intervention and a village cluster is a suitable unit for randomization. The study monitoring period will be 12 months, beginning December 2015, which will encompass one long (February-May, 2016) and one short rainy season (October–December, 2016) and two intervening dry seasons (Table 1). Following household enumeration, baseline socio-demographic, economic and household construction data will be collected. At study onset, all participating households will be provided with UC of LLINs, defined as one LLIN per every two persons. Clusters will then be randomized into two equal groups; all households in villages from one group will receive ITWL installed on interior house walls.

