**Table 1 Tab1:**
[figure not shown]
Timetable of study activities

To assess whether ITWL and UC of LLINs combined provide more protection against malaria in children than LLINs alone, a cohort of children aged 6 months to 11 years old from cluster cores will be followed monthly over 1 year. Malaria infection will be detected by malaria rapid diagnostic test (mRDT; One Step Malaria HRP-II (P.f) and pLDH (Pan) Antigen Rapid Test, Standard Diagnostics Inc., Korea) and positive children will be treated according to national guidelines. This cohort will also be surveyed for moderate (haemoglobin 7–8 g/dl) to severe anaemia (haemoglobin <7 g/dl) at enrollment, 6 months and 1 year post-intervention.

Exposure to malaria vectors will be measured indoors using Centers for Disease Control and Prevention (CDC) miniature light traps every month in eight randomly selected household in 12 study clusters/arm and outdoors using Furvela tent traps bi-monthly, in five randomly selected clusters/arm. Mosquito collections will be identified to species level and analyzed for sporozoite infection, *kdr* mutation status and blood meal source. ITWL bioefficacy will be monitored using WHO cone and cylinder bioassays and durability via High Performance Liquid Chromatography (HPLC) analysis and observational household surveys at three, six and 12 months post-intervention.

Household and community acceptability of ITWLs and LLINs will be evaluated in a series of focus group discussions (FGDs), in-depth interviews (IDIs), informal community observations and using a quantitative acceptability questionnaire before intervention and periodically throughout the monitoring year. To estimate the cost-effectiveness of ITWL and LLINs vs. LLINs alone, interviews will be conducted with residents who had a malaria incident 30 days prior, to determine the direct and indirect costs per malaria case. The cost of the intervention will be the net cost of installing ITWL and cost of malaria episodes in the study areas. The effectiveness will be the number of malaria cases averted across the age spectrum in the intervention areas, which will be assessed by collecting supplementary data from an ‘older’ sub-set of participants (≥12 years old), and will be compared to the control areas which only received LLINs.

A schematic representation of the trial is shown in Fig. 2.

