### Study intervention implementation

Prior to intervention implementation, a tiered and repetitive approach will be taken to sensitize the community to the objectives of the trial. Letters of introduction will be sent to the District Medical Officer (DMO) and District Executive Director of Muheza who will then introduce the research team to the selected study villages. Meetings will be held with these district officials, village-cluster and sub-village leaders to inform them of the study, explain the procedures and timelines and to address any questions or concerns. Because new issues can arise at any point, study staff will regularly attend community meetings throughout the monitoring period to address any problems and to provide an update of study progress.

Distribution of LLINs will be timed to occur shortly before ITWL installation in July-August, 2015, to ensure that all study households are protected before the beginning of the short rains and that participants are actively using their LLINs prior to ITWL intervention. LLINs will be distributed house-to-house, where one net will be given per every two persons. House members will be given instructions on proper use and maintenance of nets by study personnel.

ITWL installation is scheduled to begin in all buffer areas in late August 2015, to allow study teams the opportunity to remedy any unforeseen technical or logistical problems before installation in core households. ITWL installation will be rolled out in tandem with cohort recruitment. The order in which intervention clusters will receive ITWL installations will be randomized; once all eligible cohort members have been recruited in an intervention cluster and in a parallel randomly selected control cluster, ITWL will be installed in all households in the core area of the intervention cluster.

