### Entomological evaluations

The primary entomological endpoint (EIR) will be measured using CDC miniature light traps in eight randomly selected households with open eaves in 24 core cluster areas (12 clusters per study arm), every month (Table 1) [43]. Eligible households will contain children enrolled in the cohort study. In each household a CDC miniature light trap will be positioned 50 cm away from a single sleeper protected by a LLIN. To compare the extent of outdoor biting and transmission, every other month Furvela tent trapping will be undertaken in coordination with indoor light trapping [44]. One tent will be used in each cluster per night, set close to one of CDC light trapping households. Indoor and outdoor mosquito collections will be identified to species complex by microscopy [45] and the numbers of *An. gambiae* s. l., *An. funestus* s. l. and other *Anopheles* recorded. In each trap collection, a subset of *An. gambiae* s. l*.* and *An. funestus* s. l. will be speciated by PCR [46, 47]. In the case of *An. gambiae* s. l. knockdown resistance status (presence of *kdr* L1014S or L1014F alleles; previously *kdr-*east or *kdr*-west) will be determined by PCR [48]. *Plasmodium falciparum* sporozoite infection rates in *An. gambiae* s. s*., An. arabiensis* and *An funestus* s. l. will be assayed using a circumsporozoite protein (CSP) enzyme-linked immunosorbent assay (ELISA) [49].

To compare indoor mosquito resting density between the two study arms, early morning pyrethrum spray catches (PSCs) will be conducted in one household per cluster (total of 48 households). PSCs will be performed before intervention (during the long rainy season in May/June 2015), once during the cool dry season (August/September 2015) and during the second long rainy season (May/June 2016) (Table 1). To determine host feeding preferences, all blood fed malaria vectors will be squashed and dried onto filter papers and blood meal sources identified by ELISA [50].

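### The entomological sample-size section gives indoor trapping half the clusters and half the rounds that the design and methods sections give for the EIR endpoint (576 versus 2,304 household collections)

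*Protocol article*

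**What the plan says.** Three places in the protocol article describe indoor mosquito sampling.

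- **Entomological evaluations** names EIR as the primary entomological endpoint and has it measured with CDC light traps "in eight randomly selected households with open eaves in 24 core cluster areas (12 clusters per study arm), every month".
- **Design** gives the same plan: monthly light traps, eight households, 12 clusters per arm.
- **Sample size rationale, Entomological** has monitoring of indoor mosquito density "bi-monthly in eight different randomly selected households from six clusters per study arms (total of 576 households". The catch goes to speciation, sporozoite ELISA, kdr testing and blood-meal analysis.

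Two smaller statements belong with these. Entomological evaluations plans pyrethrum spray catches in one household per cluster and gives the total as 48 households. It also sends a subset of each trap's *An. gambiae* s.l. and *An. funestus* s.l. for species PCR, whereas the sample-size section has every anopheline from each household chosen at random for analysis, speciation included.

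**The concern.** A sample-size section should state the size of the study that the methods describe. Here it states a smaller one, for the sampling on which the primary entomological endpoint rests. A field team or analyst working from that section would trap in half the clusters and half as often as one working from the methods. In a comparison of arms randomized by cluster, the number of clusters largely sets the precision of the EIR ratio. The article therefore does not fix how precise that comparison is meant to be.

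The other two items are smaller. A spray-catch total that matches no stated set of clusters leaves the number of houses unclear. Two rules for which mosquitoes are speciated leave unclear how many have a known species. That matters because sporozoite rates are planned for *An. gambiae* s.s. and *An. arabiensis* separately, and these are told apart by PCR.

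**Working it through.** **1. Reproduce the stated figure.** Inputs from the sample-size section: 8 households per cluster, and six clusters per arm, so 12 in all. Design gives the duration: "The study monitoring period will be 12 months". Bi-monthly, read as every two months, gives 6 rounds.

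8 x 6 x 2 x 6 = 576, an exact match. The figure is a worked count, not a slip of the pen.

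Other readings do not remove the conflict:
- Bi-monthly as twice a month: 8 x 12 x 24 = 2,304, which contradicts the section's own 576.
- No rounds counted: 8 x 12 = 96.
- One arm sampled monthly: 8 x 6 x 12 = 576, but the text says bi-monthly and gives a total.

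**2. Count the other design.** From Design and Entomological evaluations: 8 households x 12 clusters x 2 arms x 12 rounds = 2,304 household collections.

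| | Sample-size section | Design and Entomological evaluations | Ratio |
|---|---|---|---|
| Clusters, both arms | 12 | 24 | 2 |
| Rounds | 6 | 12 | 2 |
| Household collections | 576 | 2,304 | 4 |

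**3. What the cluster number alone does to precision.** The article gives no between-cluster variation for EIR, so a CV of 0.5 to 1.0 is assumed. With c clusters per arm, SE(log ratio) = sqrt(2 x CV² / c), and the 95% limits are the estimate multiplied and divided by exp(t x SE), with t on 2c − 2 degrees of freedom.

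| CV | c = 12: SE | c = 12: factor (t = 2.074) | c = 6: SE | c = 6: factor (t = 2.228) |
|---|---|---|---|---|
| 0.5 | 0.204 | 1.53 | 0.289 | 1.90 |
| 0.8 | 0.327 | 1.97 | 0.462 | 2.80 |
| 1.0 | 0.408 | 2.33 | 0.577 | 3.62 |

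This formula has no term for the number of collections within a cluster, so it shows the effect of 12 versus six clusters and nothing else.

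**4. Adding the rounds.** With k the between-cluster CV, v the squared CV of a single collection within a cluster, and m collections per cluster, SE = sqrt(2 x (k² + v/m) / c). Here m = 8 x 12 = 96 or 8 x 6 = 48. Taking k = 0.5 and v = 10, both assumed:
- 12 per arm: sqrt(2 x (0.25 + 10/96) / 12) = 0.243
- six per arm: sqrt(2 x (0.25 + 10/48) / 6) = 0.391

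The ratio is 1.61. Over k from 0.3 to 1.0 and v from 2 to 200, the SE under the smaller design is 1.43 to 1.98 times the SE under the larger one.

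**5. Spray catches.** At one household per cluster, the 44 trial clusters give 44 per round and 132 over three rounds. The 24 light-trap clusters give 24 and 72. None is 48. That total would need 16 clusters x 3 rounds or 24 x 2, and neither is stated.

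**6. Speciation.** A subset per trap and all anophelines cannot both go to species PCR. The sample-size sentence is also at odds with itself, since choosing at random is empty if all are taken.

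**The case against.** The best defence is that the sample-size section speaks of indoor mosquito density and does not name EIR, so it might describe a separate survey. This does not stand. It describes the same eight-household indoor sampling with sporozoite testing, and no other indoor survey of that form appears; spray catches use one household per cluster. It is also the only entomological sample size given.

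Several limits on the point do stand. A reader might infer more than the article supports in these ways:

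- **A four-fold loss of precision.** Four-fold is the ratio of collections. Clusters differ two-fold, and the standard error rises by less than two-fold over the assumed ranges.
- **A null EIR result that is uninterpretable only under the smaller design.** With an observed ratio of 1 and 12 clusters per arm, the lower limit would be 1/1.53 = 0.65 to 1/2.33 = 0.43, so reductions of 35 to 57% would not be excluded. With six it would be 1/1.90 = 0.53 to 1/3.62 = 0.28, or 47 to 72%. The smaller design is worse, but neither settles the matter.
- **A tent-trap contradiction.** Design has traps "outdoors using Furvela tent traps bi-monthly, in five randomly selected clusters/arm", and Entomological evaluations says "One tent will be used in each cluster per night". The second can mean each of the five tent clusters per arm, and the frequencies agree.
- **A mistimed spray-catch round.** One round is planned "once during the cool dry season (August/September 2015", and "ITWL installation is scheduled to begin in all buffer areas in late August 2015". The article never calls that round post-intervention, gives no date for installation in core areas, and has nets distributed in July and August 2015. The round could be meant as a dry-season round around net distribution.
- **A missing power calculation or subsampling weights for EIR.** A condensed article may leave both to the full protocol or the SAP.

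The subset conflict is clear for species PCR only, because Entomological evaluations states no subset for the sporozoite ELISA.

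**Conclusion.** The point holds as an internal contradiction in a stated sample size. The size "from six clusters per study arms (total of 576 households" cannot describe the same sampling as 12 clusters per arm trapped monthly. The gap is two-fold in clusters, two-fold in rounds and four-fold in collections, and these counts need no assumption beyond reading bi-monthly as every two months, the reading that reproduces 576.

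The loss of precision is material, but its size is illustrative. The confidence factors of 1.5 to 2.3 against 1.9 to 3.6 rest on an assumed CV of 0.5 to 1.0 and on cluster number only. The spray-catch total of 48 is wrong as described, and the speciation rule is stated in two ways. The child-incidence primary endpoint and its sample size are not affected.

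**What to change.** Correct the entomological part of Sample size rationale to agree with Design and Entomological evaluations: 12 clusters per arm, eight households per cluster, monthly, 2,304 household collections. Those two sections agree with each other, and one of them defines how EIR is measured, so the third is the one to change.

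In Entomological evaluations, replace the spray-catch total of 48 with the number that follows from the clusters actually used: 44 per round if all trial clusters, 24 if the light-trap clusters. If more than one household per cluster was meant, say so.

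State one rule for which mosquitoes are speciated, and use it in both sections.

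The cost is text only. If the fieldwork follows the design and methods sections, no trapping or laboratory work changes. The speciation rule could alter the PCR workload, depending on which version was intended.

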### Data handling and record keeping

All demographic and clinical data will be collected on Android smartphones containing pre-programmed, pre-tested, standardized data entry forms, and sent directly to an electronic server. Each cohort member will have a unique identification number (ID) and non-cohort participants will be identified by a demographic enumeration number. All forms and datasets will record participants using these codes; no personal identifiers will be entered.

All data computers will be password protected with restricted access to only authorized study investigators and data management staff; field workers will have no access to the server. Daily data checks will be performed to identify incomplete, missing, inaccurate or inconsistent data, which will be rectified by the appropriate study investigator. Clinical data will be kept separately from that containing personal information. Data will be stored for at least 10 years.

The PI will maintain appropriate medical and research records in compliance with GCP and regulatory and institutional requirements. Authorized representatives of the sponsor, the ethics committee(s), the DSMB or other regulatory bodies may inspect all documents and records at any time. The PI will ensure access to facilities and records, as required.

### Data analysis

All statistical analyses will be performed using STATA version 13 (StataCorp LP, College Station, TX, USA). The primary endpoint will be a comparison of the cumulative incidence of symptomatic or asymptomatic episodes of malaria in children between the two intervention groups. Data from cohort members who are lost to follow-up or who missed monthly visit(s) will be treated as censored. Similarly, children who are taking anti-malarial drugs, based on a positive mRDT, will be excluded in the analysis for the first 2 weeks following treatment. History of travel away from the study village will be recorded during monthly visits and time at risk will be censored for such periods. In addition, malaria cases in children who resided outside their cluster area for more than half of the elapsed study period at the time of illness will be excluded.

An initial analysis will compare the cumulative malaria incidence rates between the two study arms to assess the number of episodes of malaria parasitaemia (symptomatic, asymptomatic or combined) per child per year. A follow-up analysis will examine the time to first episode of clinical malaria. The rate ratio (RR) will be calculated by dividing the incidence rate in the intervention relative to the control arm. The effectiveness of ITWL + LLINs vs. LLINs alone will be obtained from the final analysis as 1-RR. Cox regression modeling will be used to investigate potential confounding such as season and age. A priori confounders will be included in the model and that the presence of effect modification or interaction terms will be explored. Both intention to treat (all persons randomized) and per protocol analyses (all persons who received the intervention) will be conducted. All analyses will be adjusted for within-cluster correlation using generalized estimating equations or random effects models with gamma frailty. In addition, missing data will be analyzed and multiple imputation used, if required.

Similarly, mean haemoglobin in 6–59 month olds will be measured and compared between the two arms.

Other outcome variables, including entomological indices, cost-effectiveness and acceptability of interventions will be compared between study arms accounting for any correlated observations within clusters or households.

Digitally recorded FGDs and IDIs will be transcribed and translated verbatim and the data analysis procedure will follow a bottom-up approach by coding the raw data line-byline. The coding will be done by two research assistants to ensure intercoder reliability. Themes and theoretical constructs will emerge and will be grouped together as per the objectives. This method reflects a more analytical approach and will borrow the iterative approach of grounded theory analysis [60]. Data will be organized by importing into new QSR Nvivo 10 workbook and filed into the ‘internals’ section. Transcripts will be coded in an ongoing process as data is collected whereby a coding template will be developed from initial transcripts. As more data is received and coded, the template will be further refined to reflect any new emerging ideas or themes. These will appear in Nvivo as nodes which will be arranged in groups under a parent node labeled with the theme. Beyond this, themes may be organized into wider groups representing theoretical constructs. Memos will be made to explain the justification behind forming the construct. The social scientists from the project together with the wider research team will develop a narrative linking the original research objectives with the participants’ subjective practices and experiences. The aim of these theoretical descriptions will be to reiterate the participants’ narratives in terms of the theoretical constructs.

Quantitative data derived from household acceptability questionnaires will be compared using appropriate summary statistics, such as mean differences and proportions. All exposure variables showing evidence of relationships with acceptability of the study intervention in univariate analysis will be fitted in a multivariable logistic regression model. A stepwise backwards strategy will be used to eliminate variables with no effect (p > 0.05), these multilevel models will adjust for clustering within village or household and investigate for possible confounding or interaction.

Economic data collected will be used to assess the direct and indirect costs per malaria episode averted in each study arm.

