### Randomization and blinding

In cluster randomized controlled trials it is particularly important to minimize imbalance for factors known to be highly correlated with disease outcome, in this case house construction/presence of open eaves and LLIN usage. Since all households will be provided with LLINs and the majority of homes have open eaves (89 % during baseline surveys), clusters will be stratified into two groups based solely on malaria prevalence; clusters in each stratum will then be randomly assigned to the two study arms. Stratified randomization of villages will reduce the likelihood of chance imbalances between study arms but as only a relatively small number of units can be randomized in such a cluster design, both groups cannot be assumed comparable for all factors. Baseline data on malaria prevalence and haemoglobin concentration collected from all enrolled cohort participants will be used to assess disparity in disease burden at the village level prior to study monitoring.

Observer bias will be reduced where feasible; because of the visible and obvious nature of the intervention, it is not possible to conduct ITWL installation in a blinded manner. Mosquito collector bias will be reduced by using standard CDC miniature light traps and Furvela tent traps, which do not rely on the technical ability of the fieldworker to collect specimens. Trap catches will be examined by a different person to the trap collector and they will be blinded to the trap location and intervention status. The intervention implementation, for both ITWL installation and LLIN distribution, will be monitored closely for quality and to document any bias between the clusters. Epidemiological data entry will be conducted using smartphones to minimize errors in collection; GPS location and time of questionnaire administration will also be recorded to ensure that interviews are appropriately conducted and adequate time has been devoted to data collection.

Loss to follow-up will be minimized through the use of community health workers (CHWs) from each cluster to ensure children are available during monthly study visits. In the event of missing participants, the study team, assisted by CHWs, will undertake home visits to locate cohort members or may extend the monthly visits to each cluster to sample participants who are temporarily unavailable. Extended periods of time spent living away from a participant’s cluster will be recorded and factored into the analysis.

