During the ITWL intervention period, all core and buffer households will be visited 6–10 days following installation to document any AEs. Adverse event monitoring will also occur among ITWL installers through a passive AE monitoring chain. Throughout the study year, AEs will be monitored actively in each monthly cohort follow-up visit, during which the clinical team will ask the parents of cohort participants to report all AEs for any members of their household. Cohort members will also be given a study card to take to local health facilities, which will be used to record any AEs arising between monthly study visits. Other study participants will report AEs at any point to the CHWs, health facility or study team through a passive AE monitoring chain in both core and buffer areas. All AEs such as skin or eye irritation, respiratory problems, dizziness, nausea etc., will be graded in terms of severity (mild, moderate or severe), seriousness (based on patient outcome) and relatedness to the intervention by comparison with the control arm [58]. Appropriate management for any AE will be provided according to local guidelines and the outcome of AEs, including resolution, persistent disability, birth defect or death will be recorded.

In the case of a serious adverse event (SAE), the study clinician will record and manage the SAE in accordance with Good Clinical Practice (GCP) and report these to the PI who will inform the responsible member of the trial DSMB. Excessive grouping of SAEs by village or cluster will be reported to the DSMB and respective institutional ethics committees. A determination by the DSMB that there is potential harm to participants or the environment caused by the interventions will result in discontinuation of the study.

If an individual or household wants to terminate their participation, no further follow-up will be performed. If a cohort participant misses three consecutive monthly follow-up visits, they will be excluded from the study analysis. There will be no participant replacement during the surveillance period. If a household withdraws that was participating in the durability monitoring, it will be substituted with a neighbouring house of similar construction, where possible; there will be no other household or village replacements.

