### Study endpoints

#### Epidemiological

Primary endpoint: the cumulative incidence of malaria parasitaemia (asymptomatic and symptomatic) defined as the number of mRDT-confirmed episodes of parasitaemia per child per year. A child will be considered to have experienced an episode of parasitaemia during a given month if they had a positive mRDT during the scheduled monthly follow-up visit, irrespective of symptoms. Two consecutive positive scheduled mRDT results will be treated as two separate episodes and any malaria cases diagnosed and treated at health facilities between monthly visits will also be counted as episodes.

Secondary endpoints: (i) time to first episode of malaria parasitaemia (asymptomatic and symptomatic) as determined by mRDT as per the primary case definition; (ii) changes in mean levels of haemoglobin among cohort children aged 6 to 59 months.

All study outcomes will be compared between the intervention (ITWL + LLINs) and the control arm (LLINs only).

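### The long-absence rule drops malaria cases but keeps the same children's uncensored in-cluster time, so numerator and denominator of the primary rate follow different rules

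*Protocol article*

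**What the plan says.** The primary endpoint (Study endpoints, Epidemiological) is a rate, "defined as the number of mRDT-confirmed episodes of parasitaemia per child per year", and it counts positive scheduled tests whether or not the child has symptoms. In Data analysis, "The rate ratio (RR) will be calculated by dividing the incidence rate in the intervention relative to the control arm", and effectiveness is one minus that ratio.

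Four statements govern absence:

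- Data analysis, travel: "History of travel away from the study village will be recorded during monthly visits and time at risk will be censored for such periods".
- Data analysis, missed visits: "Data from cohort members who are lost to follow-up or who missed monthly visit(s) will be treated as censored".
- Data analysis, long absence, added to the travel rule: the analysis excludes "malaria cases in children who resided outside their cluster area for more than half of the elapsed study period at the time of illness".
- Trial oversight, safety considerations and handling withdrawals/drop-outs: "If a cohort participant misses three consecutive monthly follow-up visits, they will be excluded from the study analysis".

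Randomization and blinding adds only that "Extended periods of time spent living away from a participant’s cluster will be recorded and factored into the analysis", without saying how.

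**The concern.** The travel rule acts on the denominator, and the long-absence rule acts on the numerator alone. Take two children with the same travel history, each away for most of follow-up so far. If one tests positive, that case is dropped. If the other stays negative, the in-cluster time is kept as disease-free time. In-cluster time during the affected state can therefore add to the denominator but never to the numerator.

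The trigger is a share of elapsed time, so it also depends on when the absence falls. A trip early in follow-up can void a case that the same trip later would leave untouched.

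Finally, the rule is tied to the time of illness, which asymptomatic episodes do not have, although the primary endpoint includes them.

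What is at stake is the level of the incidence rates and, if affected children are more common in one arm, the rate ratio.

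**Working it through.** **Figure in the plan.** The plan gives no figure for absence. The nearest one is power above 85% (Sample size rationale). I reproduce it because it supplies the scale for judging any bias. Inputs from that section: control rate λ0 = 2.5 per year, λ1 = 0.7 × 2.5 = 1.75, between-cluster CV k = 0.302, c = 22 clusters per arm, and y = 110 × 0.82 = 90.2 children per cluster. Two-sided 5% is assumed.

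- Variance of the rate difference = [(λ0 + λ1)/y + k²(λ0² + λ1²)]/(c − 1) = [0.0471 + 0.8493]/21 = 0.0427, so SE = 0.2066.
- Power = Φ(0.75/0.2066 − 1.96) = Φ(1.67) = 95%. The stated inequality is met.
- SE of ln RR = √{[1/(λ0y) + 1/(λ1y) + 2k²]/c} = √{[0.0044 + 0.0063 + 0.1824]/22} = 0.094.

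**Bias formula.** Let q be the share of counted person-time whose cases the rule drops. With a constant malaria rate, observed rate = true rate × (1 − q), and observed RR = true RR × (1 − q1)/(1 − q0), where 1 is intervention and 0 is control.

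Suppose a share f of children is in the affected state all year, and each keeps a share s of the year after travel is censored. Then q = f·s/[(1 − f) + f·s]. At any date when the rule applies, in-cluster days are fewer than half of elapsed days. So s is below 0.5, and s = 0.5 gives an upper bound for a given f. The documents do not give f, so I assume a range.

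**Effect on one arm's rate (s = 0.5, true control rate 2.5).**

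| f | q | rate reads |
|---|---|---|
| 2% | 1.0% | 2.48 |
| 5% | 2.6% | 2.44 |
| 10% | 5.3% | 2.37 |
| 20% | 11.1% | 2.22 |

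At s = 0.25, f = 5% gives q = 1.3% and f = 10% gives 2.7%.

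**Effect on the rate ratio (s = 0.5, intervention v control).**

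| f1 v f0 | true 0.70 reads | effectiveness | true 1.00 reads |
|---|---|---|---|
| 5% v 5% | 0.700 | 30.0% | 1.000 |
| 10% v 5% | 0.681 | 31.9% | 0.972 |
| 5% v 10% | 0.720 | 28.0% | 1.029 |
| 10% v 0% | 0.663 | 33.7% | 0.947 |
| 0% v 10% | 0.739 | 26.1% | 1.056 |

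On the log scale, 0.972 is 0.028/0.094 = 0.3 of a standard error, and 0.947 is 0.054/0.094 = 0.6. At s = 0.25, 10% v 5% moves 0.70 only to 0.690.

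**A short early absence.** A child away for the first 16 days meets the condition while 16/t > 0.5, that is, until day 32. The rule voids cases in 16 in-cluster days out of 365 − 16 = 349 counted days, or 4.6% of that child's time. If 10% v 5% of children did this:

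- q1 = 0.10 × 16/(0.90 × 365 + 0.10 × 349) = 0.44%
- q0 = 0.05 × 16/(0.95 × 365 + 0.05 × 349) = 0.22%
- RR multiplier = 0.9956/0.9978 = 0.998

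The same 16 days at day 300 are 16/300 = 5% of elapsed time and void nothing. This shows both the dependence on timing and how small the effect is when the state is brief.

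**The case against.** Several points on the other side have force.

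- A reader might infer that none of these children's time is removed. That is wrong, because the sentence just before the rule censors travel. Only in-cluster time is at issue. If no time were removed, f = 10% would give q = 10%, against 5.3% at the bound above.
- The affected group is narrowed by other rules. Children who miss three visits in a row leave the analysis, and parents are asked for assurance that the child will stay resident for the year. This limits chronic absence, but a child away for 16 days early on need not miss any visit.
- A reader might infer that the rate ratio is biased. The documents give no travel data by arm and no reason why wall lining would change children's travel. That installation cannot be blinded means a difference is not excluded; it is not evidence of one.
- A reader might infer that the reported rates must come out too low. An infection acquired while away but detected after return adds a case while the away time is censored, which pushes the rate up. The rule may be meant to guard against this, so the net direction is not certain.
- The article is a condensed document, and the retained time is partly inferred from its silence. But the article does state a rule for each side of the rate, and the two do not match. Followed as written, the mismatch occurs.
- Reading the time of illness as the date of the positive test is reasonable, so that part is a matter of wording.

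**Conclusion.** The point holds in a limited form. As written, the long-absence rule excludes cases but not the same children's uncensored in-cluster person-time. The exclusion is triggered by having a case and depends on how early the absence falls. All else equal, this lowers each arm's rate, by at most about 2.6% if 5% of children were affected all year and 5.3% if 10% were.

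The rate ratio moves only if the affected share differs by arm. In the assumed scenarios with up to 10% affected, effectiveness shifts by at most about 2 to 4 points, or roughly 0.3 to 0.6 of a standard error. Where the state is brief, the shift is negligible.

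These sizes rest on assumed shares, a constant malaria rate over follow-up and the same effect of the intervention in affected children. The year-long scenarios should not be read as a forecast. Severity is moderate: this is an avoidable inconsistency in the primary analysis, not a demonstrated bias in the trial's result.

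**What to change.** Keep the sentence that censors travel time, and apply one rule to cases and person-time alike. Either option works:

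- Censor a child's person-time, and any episode detected in it, for as long as cumulative days outside the cluster exceed half of the days of follow-up so far, whether or not an episode occurs.
- Delete the case-exclusion sentence and count every episode detected in uncensored time.

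Name one as primary and report the other as a sensitivity analysis. Replace the reference to time of illness with the date of the positive test, so that asymptomatic episodes are covered. A per-interval rule that kept all time in months with shorter absences should be avoided, because it would restore travel time that the plan censors.

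The cost is wording and a few lines of analysis code. The travel history needed is already collected at each monthly visit, and the sample size is unaffected.
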